# Weight loss referrals for adults in primary care (WRAP): protocol for a multi-centre randomised controlled trial comparing the clinical and cost-effectiveness of primary care referral to a commercial weight loss provider for 12 weeks, referral for 52 weeks, and a brief self-help intervention [ISRCTN82857232]

**DOI:** 10.1186/1471-2458-14-620

**Published:** 2014-06-18

**Keywords:** Obesity, Weight-loss, Primary care, Adults

## Abstract

**Background:**

Recent trials demonstrate the acceptability and short term efficacy of primary care referral to a commercial weight loss provider for weight management. Commissioners now need information on the optimal duration of intervention and the longer term outcomes and cost effectiveness of such treatment to give best value for money.

**Methods/Design:**

This multicentre, randomised controlled trial with a parallel design will recruit 1200 overweight adults (BMI ≥28 kg/m2) through their primary care provider. They will be randomised in a 2:5:5 allocation to: Brief Intervention, Commercial Programme for 12 weeks, or Commercial Programme for 52 weeks. Participants will be followed up for two years, with assessments at 0, 3, 12 and 24 months. The sequential primary research questions are whether the CP interventions achieve significantly greater weight loss from baseline to 12 months than BI, and whether CP52 achieves significantly greater weight loss from baseline to 12 months than CP12. The primary outcomes will be an intention to treat analysis of between treatment differences in body weight at 12 months. Clinical effectiveness will be also be assessed by measures of weight, fat mass, and blood pressure at each time point and biochemical risk factors at 12 months. Self-report questionnaires will collect data on psychosocial factors associated with adherence, weight-loss and weight-loss maintenance. A within-trial and long-term cost-effectiveness analysis will be conducted from an NHS perspective. Qualitative methods will be used to examine the participant experience.

**Discussion:**

The current trial compares the clinical and cost effectiveness of referral to a commercial provider with a brief intervention. This trial will specifically examine whether providing longer weight-loss treatment without altering content or intensity (12 months commercial referral vs. 12 weeks) leads to greater weight loss at one year and is sustained at 2 years. It will also evaluate the relative cost-effectiveness of the three interventions. This study has direct implications for primary care practice in the UK and will provide important information to inform the decisions of practitioners and commissioners about service provision.

**Trial Registration:**

Current Controlled Trials ISRCTN82857232. Date registered: 15/10/2012.

## Background

Obesity has trebled since the 1980s and globally, excess weight is estimated to account for 44% of diabetes, 23% of ischemic heart disease and 7-41% of some cancers [1]. There is good evidence that intensive lifestyle interventions can produce weight loss linked to clinically significant health benefits [2], but such specialist interventions are costly given the high prevalence of obesity. Interventions delivered in primary care can also be demanding in terms of staff resources, set up and training and participant weight loss is often less than 5% of initial weight [3,4]. In the UK, NICE recommends consideration of any intervention that meets best practice, including referral to commercial weight loss programmes [5]. Commercial programmes are usually delivered in large groups by lay people, and preliminary evidence suggests they may be more affordable than interventions led by health professionals, making weight loss initiatives available for more individuals [6,7].

A number of commercial weight loss providers currently operate referral schemes for Public Health and the National Health Service (NHS) in the UK, whereby commissioners can purchase 12 week referral packages at a reduced cost, which are provided at no cost to patients. Two randomised controlled trials conducted by members of the current research team have demonstrated the effectiveness of commercial referrals. Jolly et al. compared a number of 12 week weight loss interventions in Birmingham’s Lighten Up service, including three commercial providers, to a control intervention (12 vouchers to attend a leisure centre) [8]. Twelve-month weight loss was significantly greater among participants referred to a commercial programme (Weight Watchers; WW) than control participants [−4.35 ± 6.9 kg vs −1.63 ± 6.0 kg; p < 0.001]. Jebb et al. [9] demonstrated that overweight and obese adults referred to this commercial programme by their primary care provider for 12 months lost twice as much weight as those who received standard care [−5.1 ± 6.1 kg vs 2.3 ± 4.2 kg; p < 0.001]. These findings suggest that referral to a commercial programme (CP) by a primary care provider is a clinically effective weight loss intervention over a one year period. However, limited data on participants who agreed to attend further follow up suggests significant weight regain beyond programme end [10].

The NHS currently provides 12 week referrals to commercial programmes. There is conflicting evidence on whether providing longer treatment interventions could result in greater and more sustained weight loss. In one meta-analysis of studies providing ‘extended care’ , participants receiving extended care had, on average, 3.2 kg less weight regain than controls over a mean follow up period of 17.6 months [11]. The reduced weight regain in the extended care intervention in studies with 6–12 month follow-up was at least 1.5 kg. However, in a recent review of behavioural weight management programmes, meta-regression of trials with longer and shorter programmes found no benefit of longer programmes up to 1 year [12]. Indirect comparisons from Jebb et al. and Jolly et al. suggest that 12 months CP (weight loss 5.1 kg) achieves greater loss than 12 weeks CP (weight loss 4.4 kg, assessed at 12 months). The difference is small, but participants in Jolly at al. were heavier and older than those in the Jebb et al., two factors associated with greater weight loss in an audit of the CP’s NHS referral database [13] and an observational analysis of the routine Lighten Up service [14]. Thus we might anticipate the difference in weight loss after 12 or 52 weeks intervention in comparable groups to be greater than the comparison between these two studies. Moreover, further analysis of Jolly et al. suggests the apparent impact of the WW intervention may have been atypically high. In the two other commercial providers (Slimming World and Rosemary Conley), mean weight loss at 12 months was smaller than WW, yet a much larger comparison (n = 3000) of the three providers in the routine Lighten-Up referral service shows that mean self-reported weight loss at 1 year in those attending WW was very close to the mean weight loss across all providers [14]. Mean 12 month weight loss for the three CPs in Jolly et al. was 2.7 kg, giving an assumed difference of 1.36 kg between this and the 52 weeks intervention in Jebb et al. A formal RCT is needed to show whether the greater loss in the 12 month programme is due to the longer referral and the current trial will directly compare weight loss at 12 months for participants receiving 12 weeks referral (CP12) and 52 weeks referral (CP52).

Obesity is a chronic, relapsing condition and the sustainability of weight loss achieved in short term interventions cannot be assumed. There is currently no published data on 12 week commercial referral outcomes beyond 12 months. In the limited data from participants from Jebb et al., 12 months CP did lead to greater weight loss than standard care, but this difference was small and sensitive to assumptions about missing data [10]. We will therefore follow participants up for 24 months to examine whether any initial differences in weight loss are sustained in the longer term.

Careful consideration has been given to the most appropriate control intervention. Since in many cases, obesity remains untreated in primary care, a no-intervention control may be considered to reflect standard care. However, recognition of obesity by GPs as part of recruitment to the trial and appointments for outcome measurements may constitute an intervention in its own right and in a recent review even minimal intervention ‘control’ groups lost weight [12]. Where offered, weight management interventions in primary care vary considerably. Since this is not the focus of this trial it is important to have a standardised ‘control’ intervention. Inclusion of a brief intervention based on written self-help materials will allow us to control for the impact of the GP offering a weight loss intervention and trial participation on weight loss and allow some consideration of the relative contribution of engagement and follow-up versus the nature and content of the specific intervention provided.

For NHS commissioners, one of the most important questions is whether an intervention offers value for money and a rigorous evaluation of cost-effectiveness has been built into the trial. Data on treatment costs, health-care usage and quality of life [15] will enable us to model whether any additional weight loss achieved through the 52 week programme is worth the additional costs. Initially this will consider cost-effectiveness from the perspective of the NHS, within the period of the trial (i.e. 24 months), However, ultimately, we want to know whether the interventions are likely to lead to an increase in length and quality of life, and at what cost. It is not practical to conduct a prospective study with lifetime follow up to establish this. Instead we propose using a well-developed decision-analytic model to estimate the long term impact of weight loss on risks of chronic disease and hence quality adjusted life years (QALYs) and cost.

Qualitative data suggests neither participants nor practitioners view weight management services as a priority in primary care and that some resist the idea that it is a medical issue in and of itself [16]. Thus, by delivering the intervention outside of a medical context, a CP fits better with participants’ own view of weight management. This study will examine participant experience in greater depth to explore the ways in which individuals understand and make sense of the imperative to lose weight, and the values and tensions arising from the primary care- commercial provider relationship. It will also examine the extent to which the weekly weigh in and the sense of peer support are experienced to be key aspects of the CP and the extent to which these are felt to facilitate weight loss.

Interventions for weight management could potentially be improved by developing a greater understanding of the psychosocial factors that explain individual variation in adherence, weight loss and post-intervention weight maintenance. There is a particular lack of knowledge about how these factors change during weight loss and how they affect weight maintenance. The current study will use validated questionnaires to explore a number of psychosocial factors that have either demonstrated an association with attrition, weight loss, and maintenance of weight lost in previous studies, or represent constructs identified as potentially important predictors of weight loss maintenance in recent reviews [17-19]. We will examine how baseline differences in these factors affect weight trajectories, how these factors change during and following a weight loss intervention, and how changes are associated with changes in weight.

### Objectives

#### Primary objectives

The primary research question is whether the CP interventions achieve significantly greater weight loss from baseline to 12 months than BI, and whether CP52 achieves significantly greater weight loss from baseline to 12 months than CP12.

### Secondary objectives

#### Clinical effectiveness

We will examine differences between the three interventions in weight, waist circumference, body composition, and blood pressure at 3, 12 and 24 months and differences in biochemical measures (blood glucose, total cholesterol, HDL cholesterol, LDL cholesterol, and HbA1c) at 12 months. Specifically we will test the following hypotheses:

i) Both CP interventions achieve significantly greater weight loss than BI from baseline to 3 months and baseline to 24 months and CP52 produces significantly greater weight loss than CP12 from baseline to 24 months.

ii) Both CP interventions achieve significantly greater improvements in waist circumference, body composition and blood pressure than BI between baseline and 3, 12 and 24 months.

iii) CP52 achieves significantly greater improvements in waist circumference, body composition and blood pressure than CP12 between baseline and 3, 12 and 24 months.

iv) Both CP interventions achieve significantly greater improvements in biochemical measures than BI between baseline and 12 months, and CP52 achieves significantly greater improvements than CP12.

#### Cost-effectiveness

We will examine the cost-effectiveness of each of these interventions. The following hypotheses will be tested:

i. CP52 is more cost-effective than CP12, as assessed by both within trial cost effectiveness and long term cost-effectiveness analyses.

ii. Both CP12 and CP52 are more cost-effective than BI.

### Participant experience

A qualitative workstream will explore the attitudes of participants to primary care referrals to commercial providers for weight loss, and also their wider experiences of weight management. In line with a qualitative research methodology, the following three areas will act as a guide for the research that will also remain sensitive to the experiences and topics raised by participants:

i) The extent to which participants feel that they have been referred for weight management in the NHS by their GP, and how this relates to their experience of participating in the programme and their attitudes toward weight loss.

ii) The extent to which the weekly weigh in and the sense of peer support are experienced to be key aspects of the CP

iii) The extent to which being ‘overweight’ or ‘obese’ is considered a medical issue by participants

### Psychosocial factors

This study will also examine psychosocial factors that are associated with completion of the intervention, weight loss and weight loss maintenance, to enable greater understanding of who benefits from these interventions and to inform development of new interventions.

### Biological sampling

This study will collect blood samples in order to examine changes in markers of risk of CVD and diabetes (fasting lipids, glucose and glycosylated haemoglobin). DNA will be collected for subsequent analyses of how genetic variation effects response to the interventions.

## Method

### Trial design

This is a multicentre, randomised controlled trial with a parallel design. Participants will be randomised to one of three interventions: Brief Intervention (BI), Commercial Programme for 12 weeks (CP12) or Commercial Programme for 52 weeks (CP52) in an allocation of 2:5:5 (Figure 1).

**Figure 1 F1:**
[figure not shown]
Participant flow diagram.

### Population

Overweight and obese adults (BMI ≥ 28) in the UK, deemed eligible for weight management intervention by their general practitioner.

### Setting

Participants will be recruited through primary care practices across England by three research centres. MRC Human Nutrition Research is the coordinating centre. They will recruit through local practices in Cambridgeshire and all measurements will be conducted by trained research staff at the research centre. The University of Liverpool will recruit through local practices across Merseyside and all measurements will be conducted by trained research staff at the research centre. The University of Oxford will recruit through practices across England and measurements will be conducted by trained health professionals (usually a research nurse) in the practice. Recruitment started in October 2012 and was completed in February 2014.

### Participants

Participants will be 1200 overweight and obese adults in England, recruited by their local primary care provider.

### Inclusion criteria

The inclusion criteria are BMI ≥28 kg/m2, aged ≥18 years, and willing and able to comply with the study procedures. For simplicity, we will not vary the BMI criteria by ethnic group.

### Exclusion criteria

The exclusion criteria are: planned or current pregnancy in the next two years; previous or planned bariatric surgery; currently following a weight-loss programme (defined as a structured, prescribed and monitored programme and not a self-regulated diet); non-English Speaking or with Special Communication needs that would preclude them from understanding the study materials and interventions. GP’s will exclude patients who are inappropriate to invite into the study, for example patients who are violent/terminally ill/have a history of an eating disorder. GPs will also be allowed to define any additional inclusion/exclusion criteria to meet local practice and will be asked to provide details on these for the reporting of the study. No further criteria will be imposed, thus capturing the population that would typically be referred to these treatments. Participants receiving other weight loss treatments, e.g. Orlistat, will not be excluded as such participants would still be eligible for commercial referrals in standard practice, but this will be adjusted for in the analyses. Participants will be randomised to intervention arms, and thus those receiving additional treatment should be evenly spread across the interventions and these treatments will be accounted for in the cost-effectiveness analyses.

### Inclusion of same household partners

Where more than one individual from a household is eligible and wants to enrol in the study, both members of the household will be allocated to the same treatment group (randomising participants at the household rather than the individual level) but only one person per household (the first to enrol) will be enrolled as a ‘participant’ who will provide measurements for the trial and attend follow-up visits. The ‘non-participant’ member(s) of a household will be referred to as ‘same household partner’, and will attend a ‘baseline’ visit to give consent and to receive their intervention materials. The ‘same household partner’ will be asked for consent to obtain their attendance and weight data from Weight Watchers (if they are allocated to this arm) through their WW NHS Referral Database. There is also potential for participants to be part of a household where other members are engaged in weight loss programmes, outside of this study. Therefore, all participants will be asked to provide information about weight loss activities within their household, regardless of whether they have a partner in the study or not.

### Recruitment

GP practices will be identified and recruited by the local Primary Care Research Network (PCRN). Practices will be targeted that do not have an existing contract with commercial weight loss services. In this way participants allocated to the brief intervention will not be denied standard care.

Based on the 10% recruitment rate from Jolly et al., we will approach approximately 12000 eligible individuals to recruit 1200 participants. The primary care provider will search their electronic registers for eligible individuals and GPs will screen out those to whom it would be inappropriate to send a letter (for example patients known to have a history of eating disorders or to be terminally ill). The letter will not mention the participant’s weight, but offers the availability of weight management and also will give brief details of the trial. Interested participants will be asked to telephone (on a designated Freephone number) or email the study co-ordinator at their local site for further information. A member of the research team will then describe the trial to the potential participant, undertake further screening, and, if agreeable, offer an appointment for baseline assessment and enrolment in the trial. This will be confirmed by letter, accompanied by a participant information sheet.

We will monitor uptake of the trial by ethnic group and by gender. GPs will be asked in their search for eligible participants to report summary statistics of the gender and ethnic composition of the eligible population. By comparing the recruited population to the eligible population we will be able to examine whether take-up of referral differed by ethnicity or gender.

### Randomisation

At the first assessment, a member of the research team trained in taking informed consent will ensure that the participant understands the trial and has read the participant information sheet. They will confirm their eligibility for the study and obtain written consent for their participation in the trial. Participant details, including baseline weight, will be entered into an online database by a member of the research team.

The database will automatically assign participants with a valid recorded baseline weight to one of three interventions (BI, CP12, CP52). The randomisation sequence was generated by the trial statistician and allocates participants in a 2:5:5 allocation stratified by centre and gender, with a block size of 12. The sequence is unknown to research staff and participants.

Due to the nature of the intervention and the trial design, neither participants nor research staff will be blinded to the intervention allocation.

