### Brief intervention

The control intervention is a standardised brief intervention: recognition of the problem by the GP (letter of invitation), basic written information on self-help weight loss strategies provided by a member of the research team at the baseline visit (British Heart Foundation Booklet: So you want to lose weight… for good) and weighing at follow up (coincides with outcome measurements at 3, 12 and 24 months).

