### Clinical measurements

All clinical measurements will be made in line with standardised operating procedures by trained research staff. Participants will be asked to remove shoes and heavy clothing items. Height (cm) will be measured in cm using a stadiometer. Weight and fat mass will be measured in kg using a Tanita segmental body composition analyser. Waist circumference (cm) will be measured using a tape measure, half way between the lowest rib and the iliac crest. Blood pressure will be measured using standardised methods.

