### Research dissemination and data preservation for sharing

The investigators will analyse data according to pre-defined analysis plans in a timely manner. For those analyses described in this proposal this will be within the lifetime of the grant. The PI shall ensure that the results of the trial will be submitted for publication in a peer reviewed journal, regardless of the outcome. Authorship of publications will be determined by ICMJE guidelines. As project partners, Weight Watchers understand that they will have no influence on the data analyses or publications, but they will be able to see publications 14 days prior to submission to check any factual information relating to the company. All scientific papers and reports are peer reviewed by the HNR Research Review Board and signed off before publication. A lay summary of the research findings will also be sent to participants and participating primary care practices at the end of the study.

MRC HNR will be custodians of the data resulting from the study and will ensure compliance with the Data Protection Act and the MRC policy for data sharing and preservation. The HNR database manager will take responsibility for data curation and archiving and all data sets will be kept securely with no access from unauthorised personnel. Data will be stored so that it can be accessed, used and understood by subsequent users. When the investigators have completed their planned analyses, the anonymised data will be made available for use by others and will be shared under appropriate data sharing agreements. Primary data and the Trial Master File will be retained securely in their original form for a minimum of 10 years.

The commercial programme intervention will be delivered by an employee of company and the company will provide data on meeting attendance and website usage, but they will have no role in the study design, data analysis, data interpretation, or writing of the report.

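### The reason given for leaving research staff unblinded does not cover those who measure at follow-up, so tape-measured waist (and blood pressure, if not automated) is exposed to avoidable observer bias

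*Protocol article*

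**What the plan says.** All quotations are from the protocol article.

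- **Blinding.** Randomisation: "Due to the nature of the intervention and the trial design, neither participants nor research staff will be blinded to the intervention allocation". The Trial steering committee section repeats that the study is not blinded. Neither place mentions a masked outcome assessor.
- **Who measures.** Clinical measurements: "All clinical measurements will be made in line with standardised operating procedures by trained research staff". Under Setting, research-centre staff measure at two centres. At the third, "measurements will be conducted by trained health professionals (usually a research nurse) in the practice".
- **How outcomes are read.** Waist: "Waist circumference (cm) will be measured using a tape measure, half way between the lowest rib and the iliac crest". Blood pressure: "Blood pressure will be measured using standardised methods", with no device named. Weight and fat mass: "Weight and fat mass will be measured in kg using a Tanita segmental body composition analyser".
- **Who delivers the interventions.** "The commercial programme intervention will be delivered by an employee of company", at local meetings that participants attend with vouchers. The brief intervention is "basic written information on self-help weight loss strategies provided by a member of the research team at the baseline visit", together with the GP's invitation letter and weighing at the follow-up visits.
- **Status of the outcomes.** Waist and blood pressure are secondary outcomes at 3, 12 and 24 months. Secondary hypotheses (ii) and (iii) are directional: both commercial arms better than BI, and CP52 better than CP12.
- **What else happens at the visit.** Under Adherence, attendance at the commercial programme is self-reported at assessment appointments, and BI participants report their use of the self-help materials. Table 1 lists intervention-usage questionnaires at every visit.

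**The concern.** One sentence gives one justification for two groups. Participants cannot be blinded to whether they attend a commercial programme. Measurers are in a different position: at follow-up they deliver nothing that differs by arm.

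The distinction matters most for an outcome that the observer can influence. With a tape, the result depends on finding the landmark, on tension and on the reading. A measurer who knows the arm and the hypotheses can shift readings without intending to. Such a shift would favour the hypothesised order, and it would not shrink as the sample grows. It could also look like independent support for the weight result.

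**Working it through.** **1. Does the stated reason reach the follow-up measurers?** It has two halves.

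- *Nature of the intervention.* The company runs the meetings. Research staff hand over materials at the baseline visit. Weighing at follow-up is part of the brief intervention, but all arms are weighed at the same visits, so the measurer need not know the arm to do it.
- *Trial design.* The article does not say which design feature prevents masked measurement. A parallel-group design does not. Staff who enter the baseline data, receive the allocation from the database and hand over materials must know it. That is a baseline task.

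So the reason covers participants and allocating staff. It does not cover measurement at 3, 12 and 24 months.

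**2. Which outcomes are exposed?**

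| Outcome | Method stated | Exposure |
|---|---|---|
| Weight (primary), fat mass | Body composition analyser | Small |
| Waist | Tape at a defined landmark | Yes |
| Blood pressure | Standardised, device not named | Depends on the device |

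**3. Do the plan's own figures change?** No. A normal approximation with SD 6 kg reproduces them. Stage 1 (200 v 1000, 2.3 kg, one-sided 5%) gives 99.95%. Stage 2 (500 v 500, 1.3 kg, two-sided 5%) gives 92.87%. The product is 92.82%. Masking measurers alters none of these.

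**4. How large could the effect on waist be?** The article gives neither an SD for waist change nor a size of observer bias, so this is an illustration. Assume no true difference, an SD of 7 cm, and a differential reading bias *b* between the compared groups. The planned group sizes are 200, 500 and 500.

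SE = SD × √(1/n₁ + 1/n₂)

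Rejection probability of a two-sided 5% test = Φ(−1.96 + b/SE) + Φ(−1.96 − b/SE)

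Full follow-up:

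- Combined CP v BI: SE = 7 × √(1/1000 + 1/200) = 0.542 cm. With b = 0.5 cm, b/SE = 0.922 and the rejection probability is 15%.
- CP52 v CP12: SE = 7 × √(2/500) = 0.443 cm. With b = 0.5 cm, b/SE = 1.129 and the rejection probability is 20%.

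The Discussion expects a substantial number of incomplete follow-ups, so the calculation is repeated with an assumed 30% loss in each arm. Each SE is divided by √0.7:

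- Combined CP v BI: SE = 0.648 cm, b/SE = 0.772, rejection 12%.
- CP52 v CP12: SE = 0.529 cm, b/SE = 0.945, rejection 16%.

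Sensitivity to the assumptions (two-sided 5% test):

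| Assumed SD | Bias | Follow-up | CP v BI | CP52 v CP12 |
|---|---|---|---|---|
| 5 cm | 0.5 cm | full | 25% | 35% |
| 7 cm | 0.5 cm | full | 15% | 20% |
| 9 cm | 0.5 cm | full | 11% | 14% |
| 7 cm | 0.5 cm | 70% | 12% | 16% |
| 7 cm | 1.0 cm | full | 45% | 62% |
| 7 cm | 1.0 cm | 70% | 34% | 47% |

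With no bias the rate is 5% in every row.

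**The case against.** The case on the other side is substantial.

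- **Open status is disclosed.** The article says so twice, consistently, and never claims masked assessment. This stands: nothing is concealed or contradictory. The fault is that a stated reason is applied to staff whom it does not cover.
- **The visits collect arm-specific information, and participants can disclose their arm.** This stands as a limit on what masking achieves. It bears on the order of the visit and does not show that the measurer must know the arm when the tape is read.
- **Some staff must know the arm.** This is correct. A statement that only participants are unavoidably unblinded would be inaccurate.
- **Waist is partly protected already,** by trained staff, standard operating procedures and a defined landmark. These reduce random error and some drift. They do not remove the effect of knowing the arm.
- **Visit order and staff roles may be set in operating procedures that are not shown.** This is fair, and the absence of a stated order is not itself the point. The point is the explicit rule that research staff are unblinded.
- **The percentages rest on assumed inputs.** This is also correct, and they are labelled accordingly.

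Three stronger readings are tempting, and the article does not support them. A reader might infer that the primary result is compromised, but weight is read from an instrument. A reader might treat blood pressure as observer-dependent like waist, but no device is named and an automated one would lower the exposure. A reader might take the percentages as the trial's actual error rates, but nothing in the article shows that a bias of any given size occurs.

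**Conclusion.** The point holds in a limited form. The justification supports unblinded participants and allocating staff, but not unblinded follow-up measurers. Waist circumference, a secondary outcome with directional hypotheses, is exposed to observer bias that could be reduced cheaply. Blood pressure shares the exposure only if it is not taken with an automated device. The primary comparison and the sample size are little affected or unchanged.

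For scale only: a 0.5 cm differential bias with an SD of 7 cm and no true difference would raise a nominal 5% to about 12-15% (combined CP v BI) and 16-20% (CP52 v CP12). The lower end assumes 30% loss and the upper end full follow-up. SD, bias and loss are all assumptions. The conclusion rests on the gap between the stated reason and the measurers' role, not on these figures. It merits a change because the remedy is inexpensive.

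**What to change.** 1. Where feasible, keep the allocation off the database view that the measurer uses at follow-up.
2. Take waist and blood pressure before any intervention-usage questions or discussion.
3. Ask participants not to disclose their arm until the measurements are recorded. The article already asks commercial-arm participants not to mention the trial at meetings, so a request of this kind is familiar.
4. Record at each visit whether the measurer knew the arm, and state whether the blood pressure device is automated.
5. Reword the Randomisation sentence so that unavoidable unblinding is limited to participants and to the staff who allocate and hand over materials.
6. Report the remaining lack of assessor masking as a limitation for waist and, if relevant, blood pressure.

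**Cost.** A database view setting, a visit order, a short request to participants and one tick-box, with no extra staff. Masking will be partial, especially where one practice nurse does both baseline and follow-up. Recruitment ran from October 2012 to February 2014 and the article appeared in June 2014. Visits already completed therefore stay unmasked, and a change would mix masked and unmasked visits. The record in step 4 lets the analysis show this. At publication, the later 12-month visits and all 24-month visits were still to come.
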